## Abstract

**Introduction:**

Endovenous therapy is the first choice management for symptomatic varicose veins in NICE guidelines, with 56–70 000 procedures performed annually in the UK. Venous thromboembolism (VTE), including deep vein thrombosis (DVT) and pulmonary embolism (PE), is a known complication of endovenous therapy, occurring at a rate of up to 3.4%. Despite 73% of UK practitioners administering pharmacological thromboprophylaxis to reduce VTE, no high-quality evidence supporting this practice exists. Pharmacological thromboprophylaxis may have clinical and cost benefit in preventing VTE; however, further evidence is needed. This study aims to establish whether when endovenous therapy is undertaken: a single dose or course of pharmacological thromboprophylaxis alters the risk of VTE; pharmacological thromboprophylaxis is associated with an increased rate of bleeding events; pharmacological prophylaxis is cost effective.

**Methods and analysis:**

A multi-centre, assessor-blind, randomised controlled trial (RCT) will recruit 6660 participants from 40 NHS and private sites across the UK. Participants will be randomised to intervention (single dose or extended course of pharmacological thromboprophylaxis plus compression) or control (compression alone). Participants will undergo a lower limb venous duplex ultrasound scan at 21–28 days post-procedure to identify asymptomatic DVT. The duplex scan will be conducted locally by blinded assessors. Participants will be contacted remotely for follow-up at 7 days and 90 days post-procedure. The primary outcome is imaging-confirmed lower limb DVT with or without symptoms or PE with symptoms within 90 days of treatment. The main analysis will be according to the intention-to-treat principle and will compare the rates of VTE at 90 days, using a repeated measures analysis of variance, adjusting for any pre-specified strongly prognostic baseline covariates using a mixed effects logistic regression.

**Ethics and dissemination:**

Ethical approval was granted by Brent Research Ethics Committee (22/LO/0261). Results will be disseminated in a peer-reviewed journal and presented at national and international conferences.

**Trial registration number:**

ISRCTN18501431.

STRENGTHS AND LIMITATIONS OF THIS STUDYThe primary outcome holds clinical significance.Using venous thromboembolism prophylaxis may be associated with adverse clinical outcomes, increased risks and may not be cost-effective.Due to the 90-day follow-up period, long-term efficacy of the intervention will not be assessed.

## Introduction

Varicose veins, also known as superficial refluxing veins, affect up to 45% of the UK population.^1^ Varicose veins not only reduce physical and mental health-related quality of life but also contribute significantly to chronic venous disease, which is responsible for over half of all cases of leg ulcers.^2–4^ Superficial endovenous treatment (SET) offers a minimally invasive approach that can conveniently be performed in an outpatient setting.^5^ Endovenous surgery stands as the recommended first choice management for symptomatic varicose veins, in line with NICE guidelines (CG168).^5^ This recommendation aligns with the European Society for Vascular Surgery Clinical Practice Guidelines, providing a level I recommendation for endovenous techniques.^6^ SET not only improves quality of life and facilitates venous ulcer healing but also offers cost savings to healthcare providers.^7–13^ Annually, approximately 30 000 endovenous varicose vein procedures are carried out within the NHS, a number estimated to reach 68 800 with full adherence to NICE guidelines.^14^ Additionally, an estimated 30 000–40 000 procedures are undertaken annually in the private sector.

Despite its efficacy, SET is associated with thrombotic complications, presenting occurrences of venous thromboembolism (VTE) and endothermal heat-induced thrombosis (EHIT) at rates as high as 3.4%. VTE, encompassing deep vein thrombosis (DVT) and pulmonary embolism (PE), is a significant cause of disability and subsequent societal economic consequences.^15^ Hospital-acquired thrombosis (HAT), which is defined as the development of VTE within 90 days of a hospital episode, significantly contributes to morbidity and mortality, with statistics indicating a rate of 57 deaths per 100 000 admissions within the NHS.^16^ Complications following a DVT are substantial, with up to 50% of patients developing post-thrombotic syndrome (PTS), characterised by chronic leg pain, oedema and skin changes.^17 18^ Additionally, PE is associated with lifelong functional and psychological repercussions, ultimately posing a risk of death during the index event.^19 20^ EHIT, encompassing any thrombus forming within 4 weeks of endovenous ablation and extending from the treated vein towards or into a deep vein, is categorised into four classes. EHIT classes 3–4 involve significant thrombus extension into and encompassing the deep vein, often necessitating treatment similar to that for DVT.^9 10^ SET presents a unique VTE risk compared with other short-stay surgical procedures, exhibiting a VTE rate comparable to that observed in major joint surgeries.^16^ Comparable day-case surgical procedures such as inguinal hernia repair or laparoscopic cholecystectomy exhibit a notably lower VTE rate of 0.3%.^21^

In attempting to reduce the risk of VTE, UK clinicians exhibit varying approaches: 52% routinely prescribe a single dose of low-molecular-weight heparin (LMWH) and 15% routinely prescribe extended pharmacological thromboprophylaxis with either LMWH or direct-acting oral anticoagulant (DOAC), while 33% do not prescribe any pharmacological thromboprophylaxis.^22^ These practices align with findings from a 2019 national survey of vascular surgeons in Ireland, indicating that 73% of practitioners routinely prescribe pharmacological thromboprophylaxis for SET, using either a single dose of LMWH or an extended prophylaxis, while 27% of practitioners do not prescribe any form of pharmacological thromboprophylaxis.^23^ Contradicting NICE guidelines, the routine use of pharmacological thromboprophylaxis for SET has become prevailing practice, despite having no supportive evidence base. A systematic review and meta-analysis published in 2022 failed to identify any high-quality evidence to support current pharmacological thromboprophylaxis strategies in this group of patients.^24^ However, the study suggested that there is a significant reduction in the rate of DVT with additional pharmacological thromboprophylaxis (1.09% vs 3.20% for pharmacological thromboprophylaxis vs compression alone). International and national guidelines reflect the paucity of evidence in this area, with the European Society of Vascular Surgery guidelines providing a (IIa B) recommendation for consideration of individualised thromboprophylaxis strategies.^6^ This is exacerbated by NICE NG89 recommending that ‘prophylaxis is generally not needed for people undergoing varicose vein surgery’ if their VTE risk assessment deems them low risk.^25^

Clinicians also lack confidence in current risk assessment tools (RATs) for patients undergoing SET.^15^ Despite the utilisation of RATs such as the Department of Health Risk Assessment (DHRA) Tool in the UK and the Caprini RAT in Europe and the USA, none have undergone validation for varicose vein procedures. Consequently, varicose vein intervention-specific RATs have emerged, yet these, too, lack validation. Thus, there is currently no consensus on which risk factors provide clinical indication for pharmacological thromboprophylaxis or confer high risk for VTE.^26^

Pharmacological thromboprophylaxis presents potential clinical and cost benefits in VTE prevention; however, grade A evidence is required to either support or refute this practice. Furthermore, as current RATs have not been validated in this patient group, unbiased prospective evidence will help guide risk-stratifying patients in the future. This research question also aligns with the James Lind Alliance priority setting for venous disease, further underlining the need for this trial.

### Objectives

The aims of this study are to establish whether in patients undergoing SET:

A single dose of pharmacological thromboprophylaxis decreases the risk of VTEAn extended course of pharmacological thromboprophylaxis decreases the risk of VTEPharmacological thromboprophylaxis is associated with an increased rate of bleeding eventsProviding pharmacological prophylaxis is cost-effectiveAny pharmacological thromboprophylaxis affects the rate of VTE

## Methods and analysis

### Trial design

This is a multi-centre, assessor-blind randomised controlled trial with a superiority comparison. The primary outcome is assessed blindly.

### Study setting

This trial will take place in NHS hospitals and private clinics delivering endovenous varicose vein procedures under local anaesthesia. Recruitment centres will need to have a pre-existing practice prior to the trial to prevent any learning curve effects.

### Eligibility criteria

Inclusion criteria are: adult patients (>18 years) scheduled to undergo endovenous intervention of truncal varicose veins under local anaesthesia. Treatment technologies include radiofrequency, laser, mechanochemical, foam sclerotherapy and cyanoacrylate glue.

Exclusion criteria are: clinical indication for therapeutic anticoagulation (eg, atrial fibrillation, previous personal or first-degree relative history of VTE, thrombophilia). Also female patients of childbearing potential with a positive pregnancy test, those with a history of allergy to heparins or DOACs, a history of heparin-induced thrombocytopaenia in the last year, inherited and acquired bleeding disorders, evidence of active bleeding, concomitant major health problems such as active cancer and chronic renal and/or liver impairment, known thrombocytopaenia (platelets known to be less than 50×10^9^/L), surgery or major trauma in the previous 90 days, recent ischaemic stroke in the previous 90 days, inability to provide consent.

### Interventions

There are currently three thromboprophylaxis strategies used across the UK, with the trial arms of this application mirroring these practices.^23^ Intervention arms will consist of a single prophylactic dose of LMWH (eg, dalteparin sodium, tinzaparin sodium, enoxaparin sodium) plus compression as per local practice (eg, stockings, bandages, wraps, pads) and a single dose of LMWH plus extended thromboprophylaxis with LMWH or a DOAC (eg, rivaroxaban, apixaban, dabigatran etexilate) plus compression. The choice between LMWH and DOAC for the extended thromboprophylaxis arm will be site-specific and dependent on local practice. The duration of this must be at least 7 days, but can be in line with local practice, that is, between 7 and 14 days in duration. The control arm will consist of compression (bandages, stockings, wraps or padding) as per local practice alone. The participant flow in the trial is displayed in figure 1.

**Figure 1 F1:**
[figure not shown]
THRIVE study flow chart. DHRA, Department of Health Risk Assessment; DOAC, direct-acting oral anticoagulant; DVT, deep vein thrombosis; ICER, incremental cost-effectiveness ratio; LMWH, low-molecular-weight heparin; VTE, venous thromboembolism.

### Primary outcome

Imaging-confirmed lower limb DVT with or without symptoms, or PE with symptoms within 90 days of varicose vein treatment.

### Secondary outcomes

The secondary outcomes include:

Individual components of the composite outcomeComparisons of quality of life at 7 and 90 days post-procedure using the EQ-5DMortality rates in each groupCost-effectiveness of providing pharmacological thromboprophylaxisExploratory analyses to assess how well the DHRA tool and Caprini score predict outcome

### Safety outcomes

Safety monitoring includes any bleeding event. Major bleeding is defined as per the International Society on Thrombosis and Haemostasis standardised definition,^27^ which includes:

Bleeding into a critical organBleeding into a surgical site requiring re-operationBleeding that leads to presentation to acute service

### Sample size and study duration

The most comprehensive evidence from 52 studies suggests that the rate of VTE (encompassing DVT, PE, EHIT) post-endovenous great saphenous vein interventions is 1.7%.^1^ However, this analysis did not investigate treatment effects. To address this, we conducted an analysis of 229 study arms, pooling data from 480 581 participants undergoing endovenous interventions. Our approach involved subgroup analyses, comparing those receiving pharmacological thromboprophylaxis and compression versus compression alone, and distinguishing between asymptomatic screen-detected and symptomatic VTE.^24^

For individuals receiving pharmacological thromboprophylaxis (either single dose of LMWH or extended duration), rates of DVT, PE and EHIT 3–4 were 0.521%, 0.216% and 0.354%, respectively, resulting in a maximum summary VTE rate of 1.09%. Those receiving compression alone showed rates of 2.264% for DVT, 0.058% for PE and 0.878% for EHIT 3–4, resulting in a maximum summary VTE rate of 3.20%. Rates of EHIT and DVT are distinct in this calculation, thus the impact of double counting contributing events will be negligible. In the subset data from RCT arms alone, rates of DVT were similar. When interpreting these figures in the context of the wider literature, balancing this with confounding by indication and acknowledging that VTE rate will likely be lower in the compression alone arm due to the exclusion of individuals at the highest risk of VTE, we anticipate that the true value lies nearer to 1.0% in the pharmacological thromboprophylaxis arm and 2.7% in the compression alone arm.

At 90% power and 2.5% alpha (to approximately control overall alpha to 5%, with two active drugs being compared with a common control), the study could detect a significant change of 1.7% in 90-day VTE. This base case would require 1554 participants per group. Allowing for 10% crossover (which can only be control patients, compression only, receiving pharmacological thromboprophylaxis, since everyone receives compression) increases this to 1919 per group. Allowing for a single interim analysis at half time (50% randomised with 90-day follow-up) for early stopping, for either futility or overwhelming evidence of efficacy analysis, inflates this to 1998 per group, under a two-sided, asymmetric group sequential design implementing the non-binding Hwang-Shih-DeCani spending function (lower bound (futility) with gamma-2; upper bound (efficacy) with gamma= −4).^28^ If we then allow 10% for loss to follow-up, the total sample, randomised 1:1:1 between all groups, becomes 6660 (or 2220 per group).

We will more accurately estimate the required sample size by simulation in a sample size re-estimation step at around 20% mature data, using Dunnett’s three-arm design with a common control, with correction, but for simplicity retaining the 1:1:1 equal randomisation and inputting the observed missing data proportion at that stage.

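### The fixed 2.5% per comparison is valid, but a step-down test at the same overall 5% would give more power with no extra participants

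*Protocol article*

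**What the plan says.** The section on sample size and study duration sets the error level and the family it covers: "At 90% power and 2.5% alpha (to approximately control overall alpha to 5%, with two active drugs being compared with a common control". The family is therefore two comparisons, each active arm against compression alone, at 2.5% each. The same section builds this into a design described as "under a two-sided, asymmetric group sequential design implementing the non-binding Hwang-Shih-DeCani spending function".

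The planning assumption is that "the true value lies nearer to 1.0% in the pharmacological thromboprophylaxis arm and 2.7% in the compression alone arm", and the section says that "the study could detect a significant change of 1.7% in 90-day VTE". It continues: "This base case would require 1554 participants per group". Crossover "increases this to 1919 per group", the interim analysis takes it to 1998, and loss to follow-up to 2220 per group, 6660 in all.

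The section also plans to re-estimate the sample size at about 20% mature data with a Dunnett three-arm design and common control. That method is stated for re-estimation, not as the final test.

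The Objectives list five aims. Three concern VTE: single dose, extended course and, last in the list, whether any "pharmacological thromboprophylaxis affects the rate of VTE". The article gives this last aim no alpha and no rank. The Statistical analyses section leaves the detail to a SAP.

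**The concern.** A fixed 2.5% for each comparison holds the second test at 2.5% even after the first has been rejected. At that point only one null hypothesis remains in the family, and testing it at 5% keeps the overall error at 5%. A step-down procedure uses this: it rejects everything the fixed split rejects, and sometimes more.

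The trial asks separately about a single dose and an extended course. If both work, the useful result is to show both. The 90% in the plan is power for each comparison; power to show both is lower, and that is where a step-down test helps most.

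The aim on any prophylaxis raises a smaller question. It lies outside the family that the alpha statement covers, so a reader of the article alone cannot tell whether it is meant to carry a confirmatory claim.

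**Working it through.** **Inputs (all from the sample size section).** Control rate 2.7%, active rate 1.0%, difference 0.017; two-sided alpha 0.025 per comparison; power 90%; allocation 1:1:1.

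**1. Reproduce the stated size.** With unpooled variance:

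- v = 0.027 × 0.973 + 0.010 × 0.990 = 0.03617
- n = (2.2414 + 1.2816)² × v / 0.017² = 1554 after rounding up, as stated
- crossover: 1554 / 0.9² = 1919
- interim: 1998, taken as stated (factor 1998/1919 = 1.041)
- loss to follow-up: 1998 / 0.9 = 2220; × 3 = 6660

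The pooled-variance formula gives 1558. The 2.5% has been applied correctly.

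**2. Family-wise error of the fixed split.** With equal arms and a shared control, the two test statistics have correlation 0.5 under the global null. The bivariate normal integral at |z| > 2.2414 gives 4.65%, against the Bonferroni bound of 5.0%.

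**3. Why a step-down test costs no error.** Holm tests the larger |z| at 2.5% and, only if that is rejected, the other at 5%.

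- If both nulls are true, Holm makes a first rejection exactly when the fixed split does, so the family-wise error stays at 4.65%.
- If one null is true, it is tested at 5% at most.

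**4. Power at n = 1554, before crossover and interim inflation, both arms at 1.0%.** The standardised effect is 0.017 / √(0.03617/1554) = 3.524. At these rates the correlation between the two statistics is the control arm's share of the variance, 0.02627/0.03617 = 0.73.

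| Model | Rule | Per comparison | Both |
|---|---|---|---|
| Normal | 2.5% each | 90.0% | 84.9% |
| Normal | Holm | 92.7% | 90.2% |
| Binomial simulation | 2.5% each | 91.2% | 85.2% |
| Binomial simulation | Holm | 94.0% | 91.0% |
| Binomial simulation | Step-down Dunnett | 94.2% | 91.1% |

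**5. Other scenarios (binomial simulation).**

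- One arm at 1.0%, the other at 1.5%, n = 1554: power for the weaker arm rises from 54% to 65%.
- One arm at 1.0%, the other no better than control, n = 1554: power for the effective arm is 91.2% under both rules.
- Crossover case, n = 1919, control rate 0.9 × 2.7% + 0.1 × 1.0% = 2.53%, both arms effective: per comparison 92.4% to 94.9%; both 87.2% to 92.2%.

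**6. The aim on any prophylaxis.** Suppose it were tested by pooling the two active arms against control. That statistic has correlation 1.5/√3 = 0.866 with each pairwise statistic. The simulated family-wise error over all three tests is 5.05% with the pooled test at 2.5%, and 6.6% with it at 5%.

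**The case against.** The strongest reply is that nothing here is an error. The 2.5% is a valid, slightly conservative sizing level, it delivers the stated 90%, and it stands in a sample size paragraph that need not fix the final test. The planned Dunnett step shows that the authors regard the split as an approximation, and a SAP may already specify a step-down order. The gain also depends on both arms having an effect. Most of this stands, and it is why the point is offered as an improvement. It does not remove the point: 2.5% is the only level the article gives, and the Dunnett step is tied to re-estimation of the sample size.

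A reader might also go further and infer that three VTE aims against a two-test budget leave the 5% overall error unprotected. The article does not support that:

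- It names the family as two active-versus-control comparisons.
- It does not call the aim on any prophylaxis primary or confirmatory, and it does not mention a pooled test. That aim could be answered by rejecting either pairwise null, which needs no further alpha.
- Even a pooled test at the only stated level, 2.5%, gives 5.05%, which agrees with a claim of approximate control.
- The 6.6% requires a confirmatory pooled test at 5%, which the article nowhere states.

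The rank of a supportive comparison is ordinary SAP content.

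**Conclusion.** The alpha split is valid and the sample size is right for it. The remaining point is one of efficiency: at the same overall 5%, a step-down test adds about 3 points of power per comparison and about 5 to 6 points for showing both effects, if both arms reach the planned 1.0% against 2.7%. The gain can be larger for an arm with a weaker effect, and is close to nil for an arm that is the only effective one. These figures are for a fixed design of 1554 per group without the interim look. The unranked aim on any prophylaxis needs a clarifying label and is not evidence of an inflated error rate.

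**What to change.** Keep 6660 participants. State in the SAP, before any unblinded data are seen, that the two active-versus-control comparisons form the confirmatory family at overall two-sided 5%. Test the larger |z| at 2.5% (or at the Dunnett level, about 2.70% per comparison) and, if it is rejected, the other at 5%. Apply the same spending function to the recycled alpha, so that the interim and final boundaries for the second comparison are defined in advance. If the SAP already says this, no change is needed.

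Add one sentence labelling the aim on any prophylaxis as supportive, with a 95% confidence interval and no confirmatory claim. It should not become a gate for the pairwise tests without thought: in the simulation at n = 1554, a pooled gate at 5% cut power for a lone effective arm to about 47%.

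The change costs SAP wording and no participants. The downside is in reporting. Simultaneous intervals that match a step-down test are less simple than two 97.5% intervals, and a second comparison rejected at 5% may have a 97.5% interval that includes no effect. The SAP should say which intervals accompany the test.

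### The crossover allowance wrongly rules out active-to-control crossover, so the stated 90% power holds only if almost every active-arm participant receives some drug

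*Protocol article*

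**What the plan says.** All from the protocol article.

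- **Sample size and study duration.** The planning rates are "1.0% in the pharmacological thromboprophylaxis arm and 2.7% in the compression alone arm". The test level is set by "At 90% power and 2.5% alpha (to approximately control overall alpha to 5%, with two active drugs being compared with a common control"), the target is that "the study could detect a significant change of 1.7% in 90-day VTE", and "This base case would require 1554 participants per group".
- **Same section, crossover.** A 10% allowance raises the number to 1919 per group. The parenthesis on crossover reads "which can only be control patients, compression only, receiving pharmacological thromboprophylaxis, since everyone receives compression". The interim analysis takes 1919 to 1998, and 10% loss to follow-up takes that to 2220 per group, 6660 in total.
- **Same section, source of the active rate.** One pooled figure serves both active strategies: "For individuals receiving pharmacological thromboprophylaxis (either single dose of LMWH or extended duration").
- **Same section, re-estimation.** At about 20% mature data the sample size is to be re-estimated by simulation, "inputting the observed missing data proportion at that stage".
- **Interventions.** Control is compression alone. One active arm is a single LMWH dose plus compression. The other is a single LMWH dose, then LMWH or a DOAC, plus compression; on the course, "The duration of this must be at least 7 days, but can be in line with local practice".
- **Statistical analyses and Blinding.** The main analysis is by allocated group. Clinicians and participants know the allocation.

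**The concern.** The parenthesis gives a reason for making no allowance in the active arms, and the arm definitions contradict it. The arms share compression and differ only in the drug. Take the drug away from an active-arm participant and what remains is the control treatment. Universal compression is therefore what makes crossover towards control possible; it does not exclude it.

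Such participants can arise here. Randomisation comes before the procedure, allocation is open, and the Introduction reports that 33% of UK clinicians prescribe no drug prophylaxis. Each one is analysed in the active arm at the compression-alone risk, which narrows the 1.7-point difference just as control participants given the drug do.

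What is at stake is how a null result would be read. If some active-arm participants receive no drug, a non-significant comparison could be taken as evidence against prophylaxis from a 90%-powered trial when the actual power was lower.

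**Working it through.** **Inputs.** Control rate 2.7%, active rate 1.0%, power 90%, alpha 2.5% per comparison (two-sided), control crossover c = 10%, all from the sample size section. The active-arm non-receipt rate x, meaning the proportion given no drug at all, is not in the document. It is an assumption, shown as a range.

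**Step 1: reproduce the plan's figures.**

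- Base, unpooled variance: n = (z₀.₉₈₇₅ + z₀.₉₀)² × [0.027×0.973 + 0.010×0.990] / 0.017², with (2.2414 + 1.2816)² = 12.411. This gives 1553.4, so 1554 as stated. The pooled-variance formula gives 1558.
- Crossover: 1554/(1 − 0.10)² = 1554/0.81 = 1918.5, so 1919 as stated.
- Interim: 1998/1919 = 1.041, taken as stated.
- Loss to follow-up: 1998/0.9 = 2220, and 3 × 2220 = 6660, as stated.

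The arithmetic is right. The problem lies in the premise behind the crossover step.

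**Step 2: model crossover in both directions.**

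- Control-arm rate = 2.7%×(1 − c) + 1.0%×c
- Active-arm rate = 1.0%×(1 − x) + 2.7%×x

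With c = 10% the control-arm rate is 2.53%. At x = 0 the difference is 1.53 points and the pooled formula needs 1837 per group, so 1919 carries some slack. The slack arises because 1/(1 − c)² shrinks the difference but keeps the variance of the undiluted rates.

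**Step 3: power at 1919 per group, with c = 10%.**

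| Assumed x | Active-arm rate | Difference | Power, pooled formula | Power, plan's own 1/(1 − c − x)² rule |
|---|---|---|---|---|
| 0% | 1.000% | 1.530% | 91.3% | 90.0% |
| 1% | 1.017% | 1.513% | 90.5% | 89.3% |
| 2% | 1.034% | 1.496% | 89.7% | 88.6% |
| 3% | 1.051% | 1.479% | 88.8% | 87.8% |
| 5% | 1.085% | 1.445% | 86.9% | 86.1% |
| 10% | 1.170% | 1.360% | 81.2% | 81.3% |

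With the rates modelled explicitly, power crosses 90% at x of about 1.6%. Under the plan's own rule it falls below 90% at any x above zero. Rebuilding the group sequential design at 1998 per group gives nearly the same figures: 91.4%, 87.0% and 81.4% at x = 0%, 5% and 10%.

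**Step 4: read the 10% as a total over both directions.** With c = 5% and x = 5% the rates are 2.615% and 1.085%, a difference of 1.53 points. The plan's rule gives 1554/(1 − 0.05 − 0.05)² = 1919 per group and 90.0% power; the pooled formula gives 89.9%. The stated number therefore already supports a two-way 10%, though the parenthesis excludes that reading.

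**The case against.** The strongest reply is that the document gives no non-receipt rate, so every power figure below 90% comes from a rate brought in from outside. With full receipt the number is slightly generous. The inflation factor covers ten points of dilution whichever arm they fall in, and 81% appears only when a second ten points are added to the stated ten. All of this stands. It limits the point to a false premise with a conditional consequence, but it does not rescue the premise.

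Three stronger readings are tempting, and the document does not support them.

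- **Stopping the extended course early dilutes the comparison.** A reader might infer this from a course of at least 7 days. But the extended arm begins with a single LMWH dose, so a participant who takes it and then stops has had the single-dose regimen, not control. The plan assigns 1.0% to both active strategies, so on its own assumptions this causes no dilution. Only participants who receive no drug at all count.
- **The 1.0% rate contains no non-receipt.** The source rates are described as those of people receiving prophylaxis. Whether the pooled arms were classified by allocation or by actual receipt cannot be told from the article.
- **The re-estimation would miss the problem.** Missing data is the one observed input named, but the text does not say it is the only one, and an article may leave the full list to the full protocol or SAP.

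**Conclusion.** The point holds in a limited form. The stated reason for a zero active-arm allowance is false by the protocol's own arm definitions, and the sample size relies on it. With 10% control crossover, the stated 90% power holds only if no more than about 1.6% of active-arm participants receive no drug. At 3%, 5% and 10% it is about 89%, 87% and 81%.

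A reader might infer that the trial does not deliver 90% power. The document does not show that, because the size of any loss depends on a rate it does not give. The figures assume the planning rates of 2.7% and 1.0%, the compression-alone risk for anyone given no drug, the active-arm risk for anyone given at least the first dose, and the same non-receipt rate whichever active arm is compared with control. That the premise is wrong is certain; how much power is lost, if any, is not known.

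**What to change.** 1. Delete the statement that only control participants can cross over.
2. Then do one of two things. Either state that the 10% is the total over both directions, for example 5% and 5%, for which 1919 per group gives 90.0% under the plan's own rule. Or keep 10% control crossover, state an assumed proportion of active-arm participants who receive no drug, and restate the power for it.
3. Name the observed crossover in both directions (control participants given the drug, active-arm participants given none) as inputs, alongside missing data, to the re-estimation already planned at about 20% mature data.

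The cost is a change of wording in the protocol and SAP, recording whether any drug was received where this is not already captured, and possibly a less favourable power figure. The correction needs no added patients. Whether to enlarge the trial is a separate decision, best left to the re-estimation once real rates are seen.
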